### Study design

The study was designed based on evidence from our previous study; extensive preliminary work with national data, hospital, and HHC stakeholders; & implementation science literature [24, 25, 34, 50, 60, 64–72]. The study is a pragmatic, Type 1 hybrid design, that primarily evaluates effectiveness via Aim 1, with an observational, implementation component integrated into its design via Aim 2. This novel research design is being increasingly used in the evaluation of service delivery type interventions, especially when conditions are heterogeneous and traditional randomization of individuals is not possible [73]. This pragmatic design involves an initial period in which no sites are exposed to the intervention followed by a six-month onboarding period, a 12-month intervention period, and a 6-month maintenance period. In the initial proposal we planned a stepped wedge cluster randomized trial but due to the COVID-19 pandemic the 2020 cohort are unsuitable as a comparison cohort requiring extension of the inclusion dates for the comparison dataset to 2021–2024, and staggered rollout required by stepped wedge design is no longer feasible to finish the study on time.

Sepsis survivors transitioned to the participating HHC agencies during the period before implementation serve as the usual care control group compared to those exposed to I-TRANSFER, the intervention group. To address historical threats and to increase generalizability, we form control comparison groups from national Medicare clinical and administrative claims data within and outside our partner sites to compare to our intervention group: 1) one year prior to any contact with our team; 2) during the onboarding period, and 3) across the entire study period. Observations on survivors from outside our partners’ sites will be weighted using entropy balancing [74–76] to produce a covariate-balanced comparison group.

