### Study period

Onboarding is a 6-month period when the implementation and research teams plan the implementation. Intervention is the 12-month period when I-TRANSFER is in operation. Maintenance is a 6-month period when the research team assesses whether the intervention continues without research team monitoring and feedback. The analysis will be an intent to treat. We will adjust for time, or any health system interventions, as well as patient covariates that may confound the findings using generalized mixed models.

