### Data sources and collection

#### Aim 1, effectiveness of the I-TRANSFER intervention

A national sample of Medicare administrative, home health OASIS and claims data from CMS Chronic Condition Warehouse (CCW) will be employed (Table 1). This will yield detailed information about the index hospital stay, subsequent HHC and outpatient provider services and outcomes. It also will provide information about the characteristics of hospitals and admitting HHC agencies, and the health care market areas where patients live. The CCW maintains calendar year files so we will request files between 01/01/2021 and 12/31/2024. We will request CCW data on all Medicare beneficiaries with a claim for a HHC service provided one year prior to the start of the study to 6 months after the end. Within these data sets, we will identify the sepsis survivors transitioned from participating hospitals to their partner HHC agency by merging the Provider of Service File with the claim files. The additional sepsis survivors found in the CCW data, not associated with our participating institutions, will serve as additional controls.

**Table 1 Tab1:** Variables Obtained from the Medicare Claims and OASIS Home Health Admission Files

Data	Source
*Physician, Home Health Agency and Hospital Characteristics*	
Physician specialty	Downloadable National Provider Identifier File (CMS)
Home Health Agency and Hospital Ownership	Provider of Services File
Home Health Agency and Hospital Control/auspices (for- profit/non-profit/public)	Provider of Services File
Size of home health agency, # of annual admissions	Provider of Services File
*Beneficiary Sociodemographic, Clinical and Cost Variables*	
Demographics	Medicare Beneficiary Summary File; OASIS
Informal support	OASIS
Living arrangements	OASIS
Eligible for Medicare and Medicaid	Medicare Beneficiary Summary File
Health care use and cost (ie. Medicare program payments)	MedPAR/Medicare Parts A and B SAF claims
Medical diagnoses ICD codes, acute and HHC	MedPAR/Medicare Parts A and B SAF claims; OASIS
Index hospital length of stay	MedPAR
Cognitive, physical, sensory function	OASIS
*Early Nursing and Outpatient Provider Visits Following Index Hospital Discharge*	
Timing and number of home health visits	Medicare Home Health SAF claims
Timing of first physician, physician assistant or nurse practitioner visit for outpatient evaluation & mgt	Mediare Part B SAF claims

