**Objective 6. Determine the process for how home health activates timely visits**
How do you implement timely home visits (defined as: visits within 48 h of hospital discharge)?
1. What people are involved in scheduling the home health care admission visit?
2. Do the home health agency personnel know the expected hospital discharge date?
3. What conflicts arise when trying to schedule timely home health admission visits?
4. What IT tools are used?
5. What criteria is used to prioritize patient visit timing?
6. How is start of care visit timing monitored?
7. What is your current success rate for making the admission visit within 48 h of discharge?
8. What makes this difficult to do?
9. How do you think we could improve the success rate for achieving timely visits?
10. What strategies were tried and failed?
11. What works?
12. What role does geographic area play?
13. What role does the day of the week play?
14. What role does staffing play?
15. Is patient acceptance of timely visits a barrier? (just got home from hospital, don’t want you to visit)
16. To make improvements in this process, who should we work with?

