### Analysis

#### Aim 1, effectiveness of the I-TRANSFER intervention

A key initial task is the identification of all sepsis survivors in the national hospital dataset. Consistent with our prior work, we will use two complementary strategies to identify sepsis survivors. First, we will use the explicit International Classification of Diseases 10th Revision (ICD-10) codes (A40-41, R65.2). Second, we will employ the implicit approach used in our previous study and developed by Angus and colleagues [88] that requires a code for infection and end-organ dysfunction. Among them we will identify the sepsis survivors transitioned from participating hospitals to their partner HHC agency during the study timeframe by merging the Provider of Service File with the claim files.

Each hospital discharge of a sepsis survivor to HHC will represent a separate record on the timeline file. Some Medicare beneficiaries will have more than one index hospital discharge during the study period. Data available will give us the flexibility to define an “index” hospitalization in several ways. Our main approach will be to analyze all eligible hospitalizations followed by HHC and to adjust for the potential effect of clustering at the patient and provider level. We plan to examine the sensitivity of our results to alternative specifications of the “index” hospital stay including analyses based on a single index hospitalization per person.

Deidentified Medicare claims will be the source of information used to construct Aim 1 outcomes of rehospitalization, total hospital days if readmitted and ED utilization. The CMS claims will be stored a secure, password protected site. The CMS approach to identifying hospital readmissions was successfully used in our heart failure and sepsis studies and we will use the same approach to identify readmissions in this study [24, 50]. Observations on sepsis survivors in the baseline period will be used to check balance on covariates identified by the Andersen Behavioral Model. Any remaining imbalance will be considered by including covariates in the hierarchical regression analysis.

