In addition to the survivors from the treated dyads in the baseline period, additional control survivors will be used to provide a much larger sample of control observations. These observations will be drawn from the population of Medicare sepsis survivors not being cared for by any of the participating institutions. This sample is unlikely to be balanced on covariates, a priori, with the sample of survivors from participating providers. Therefore, entropy balancing will be used to create sampling weights for these observations to produce balance on covariates. All hierarchical regression analyses will take these entropy balance weights into account. In addition to an intent-to-treat indicator, the regression will include covariates specified by the Andersen Behavioral Model. Inpatient days after the index discharge will be modeled using hierarchical Poisson regression. ED utilization will be modeled using hierarchical logistic regression.

The pragmatic aspects of the study design make it important to conduct various sensitivity and exploratory analyses. Sensitivity analyses will include checks of robustness of findings with and without sepsis survivors who are readmitted shortly after discharge (e.g., within 7 days), those with a resumption of HHC episode, discharges with very short (1 day) or very long hospital stays (30 days or more), and survivors less than 65 years old. Exploratory analyses will include estimation stratified by type of sepsis, sex (as a biological variable), and hospital ownership status.

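### Partner-hospital survivors who go to a non-partner agency after go-live fall in no analysis group, so intent to treat holds only within the dyad cohort and a shift in agency destination would go undetected

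*Protocol article*

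**What the plan says.** The rule for the dyad cohort appears twice in the protocol article. Data sources and collection (Aim 1) says "we will identify the sepsis survivors transitioned from participating hospitals to their partner HHC agency by merging the Provider of Service File with the claim". Analysis (Aim 1) repeats it for the whole study timeframe: "we will identify the sepsis survivors transitioned from participating hospitals to their partner HHC agency during the study timeframe". Both conditions, hospital and agency, must be met.

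The controls come from two places.

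- **Internal.** Study design says "Sepsis survivors transitioned to the participating HHC agencies during the period before implementation serve as the usual care control group".
- **External.** Data sources and collection says "The additional sepsis survivors found in the CCW data, not associated with our participating institutions, will serve as additional controls". Analysis describes the same pool: "These observations will be drawn from the population of Medicare sepsis survivors not being cared for by any of the participating institutions".

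Study period states the principle: "The analysis will be an intent to treat". The Analysis section puts an intent-to-treat indicator in the regression. Background says that the intervention begins in acute care. Study design lists its hospital components: identifying the survivor, booking the outpatient visit before discharge, and notifying the agency. Study sample describes it as clinical care for all sepsis survivors.

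**The concern.** Which agency admits the patient is known only after the hospital components have started. The agency may by then have been told that the patient is a sepsis survivor who should be seen within 2 days of discharge and again that week. That could change who ends up with the partner agency, in either direction: some patients might be placed elsewhere, or more might be steered to the partner. Cohort membership thus depends on an event that the intervention can influence.

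If the patients who leave or join the partner-to-partner stream after go-live differ in readmission risk, the dyad readmission rate moves without any effect on anyone's care. The planned analysis could not show this, because the patients concerned appear in no group and no listed sensitivity analysis looks at agency destination.

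**Working it through.** **Step 1. Place one patient.** Take a sepsis survivor discharged from a partner hospital after go-live and admitted to a non-partner agency.

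| Group | Rule in the article | Does this patient qualify? |
|---|---|---|
| Dyad intervention cohort | Partner hospital and its partner agency (Data sources; Analysis) | No: wrong agency |
| Internal usual-care controls | Participating agencies, before implementation (Study design) | No: wrong agency and wrong period |
| External controls | "drawn from the population of Medicare sepsis survivors not being cared for by any of the participating institutions" (Analysis) | No: treated at a participating hospital |

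Two phrases could be read more widely. Study design speaks of controls from inside and outside the partner sites, and Analysis speaks of all eligible hospitalizations followed by home care. Neither assigns this patient to a group.

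**Step 2. Check the planned safeguards.** The sensitivity analyses listed under Analysis concern early readmission, resumption of home care, very short or long stays, and age under 65. None concerns agency destination. Entropy balancing and regression work on measured covariates of patients already included. They can absorb part of a change in case mix, but they cannot bring back patients who were dropped.

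**Step 3. Illustrate the size.** The article gives no diversion rate, so there is no figure of the plan's own to reproduce on this point. It does give a 23% usual-care readmission rate and a 7-point target (Study sample; 7/23 = 30.4%, as stated there).

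Assume no true effect and no diversion beyond the baseline pattern before go-live. Let f be the share of the partner-to-partner stream diverted after go-live, and r the readmission rate of those diverted. Then:

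- retained rate = (23 - f × r) / (1 - f)
- apparent reduction = 23 - retained rate

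Assume also that 70 of every 100 home-care sepsis discharges from a partner hospital go to the partner agency at baseline.

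| Diverted | f | r (assumed) | Retained rate | Apparent reduction |
|---|---|---|---|---|
| 5 of 70 | 7.1% | 28% | (70×23 - 5×28)/65 = 22.6% | 0.4 points |
| 5 of 70 | 7.1% | 33% | (70×23 - 5×33)/65 = 22.2% | 0.8 points |
| 10 of 70 | 14.3% | 33% | (70×23 - 10×33)/60 = 21.3% | 1.7 points |
| 5 of 70 | 7.1% | 23% | 23.0% | 0 |
| 10 of 70 | 14.3% | 16% | (70×23 - 10×16)/60 = 24.2% | -1.2 points |

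The third row is 1.7/7 = 24% of the target effect. The fourth shows no bias when diverted patients carry average risk. The last shows the sign reversing when they are lower risk, so that the intervention looks worse than it is. These are crude figures, before covariate adjustment.

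**Step 4. What a hospital-level cohort would cost as the primary analysis.** Under the same 70% assumption, suppose that patients of other agencies gain nothing. A 7-point effect dilutes to 7 × 0.70 = 4.9 points. The article's 400 per interval is close to the 396 given by a two-proportion formula for 23% against 16% with one-sided 5%, 80% power and no clustering (assumed settings; the article states none). On those settings, 23% against 18.1% needs about 840 per interval.

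**The case against.** Several points on the other side stand.

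**No diversion is documented.** A reader might infer from the needs assessment that partner agencies will turn away hard-to-schedule survivors. Objective 6 only asks questions, such as "What conflicts arise when trying to schedule timely home health admission visits", along with questions on geography, weekday and staffing. It reports no answers. The Background remark on accepting a referral concerns when an agency starts the timeliness clock, not whether it refuses patients. The challenges that Study design expects for the outpatient visit do not include refusal by the agency.

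**The rule is the same in every period.** Baseline patients sent elsewhere are dropped too. The rule alone creates no bias; a change after go-live that is related to risk is needed.

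**The comparison is not simply contrary to intent to treat.** That stronger reading is tempting, but dyad patients who never receive the timely visits stay in the exposed group. The intervention targets hospital and agency together, and Aim 1 concerns survivors receiving home care. Analysing the dyad's own patients is a legitimate choice of target population.

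**Adjustment may absorb part of the shift.** OASIS function, diagnoses, living arrangements, county supply and ZIP-level measures are all available.

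**A hospital-level primary analysis would be costly.** The dilution in Step 4, 2.1 points, exceeds the largest illustrated false reduction, 1.7 points.

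The gap itself is not answered. The article fixes the cohort rule, states a principle that reaches further than the rule, and plans nothing that would reveal a change in destination.

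**Conclusion.** The point holds in a limited form. Partner-hospital survivors who go to a non-partner agency after go-live belong to no defined group. Intent to treat is kept within the dyad cohort, but not for all survivors exposed to the hospital components. If the share or risk mix reaching the partner agency changes after go-live, the before-after comparison is biased.

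Size and direction are unknown. The range of about 0.4-1.7 points rests on assumed diversion of 7-14% at 28-33% readmission, no true effect and no adjustment. A reader might infer that the design flatters the intervention; the documents do not support that, because the bias can be zero or go the other way. This is a reason to measure agency destination, not to replace the primary cohort.

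**What to change.** 1. Keep the partner-to-partner cohort as the primary Aim 1 cohort.
2. Under Analysis (Aim 1), add a sensitivity analysis on all sepsis survivors discharged from a partner hospital to any home health agency, defined alike in the baseline and intervention periods.
3. Tabulate, by period, the share of those survivors who go to the partner agency, and their baseline characteristics.
4. Under Study period, state that intent to treat applies within the dyad cohort.

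No new data are needed: the claims request under Data sources and collection already covers all Medicare beneficiaries with a home-care claim in the window. The cost is a little more analysis. Because patients of non-partner agencies dilute the hospital-level estimate, it should be read as a check on selection and not as a rival estimate of effectiveness.

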### Study sample

#### Aim 1, effectiveness of the I-TRANSFER intervention

Sample sizes needed to provide sufficient power were calculated using Stata [79]. Preliminary unpublished data of a national sample show on average a 23% 30-day readmission rate for sepsis survivors in HHC. Our previous study showed a 7-percentage point or 41% relative reduction among those receiving early visits [24], and other studies report that 22–45% of readmissions are preventable [80]. Therefore, to detect a 7-point reduction (30.4% relative decrease) in the readmission rate under the intervention we would require an average of 400 patients per time interval. Current estimates from the sites give us 869 per period.

The I-TRANSFER intervention is targeted at the hospital and HHC agency and is considered part of clinical care implemented for all sepsis survivors. There is no individual patient recruitment, prospective assignment, or primary data collection from patients. The analysis will be completed on existing datasets. We will analyze a sample drawn from all Medicare fee-for-service sepsis survivors discharged to HHC during a 4-year period (01/01/2021 and 12/31/2024). Analyses from our 2013–14 dataset suggests that without exclusions there will be approximately 800,000 sepsis discharges per year who receive HHC [24].

Ten clinical sites located in the United States have committed to participate as dyads, 5 referring hospitals and their 5 partnered home health agencies. Sites were selected based on our relationships with staff, ownership status (hospital owned or free-standing), commitment to appoint an implementation team, size, geography, and diversity (academic and community). We sought regional diversity with sites in the East and West. To be eligible HHC agencies must be Medicare certified to generate claims and confirm a hospital referral source as a partner.

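### Clustering is adjusted at patient and provider level only, so dyad-specific change between periods, seen in just five exposed dyads, is left out of the standard error for the Aim 1 effect

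*Protocol article*

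**What the plan says.** - **Exposed units.** Methods, Study sample, Aim 1: "5 referring hospitals and their 5 partnered home health agencies".
- **Schedule.** Study design describes "an initial period in which no sites are exposed to the intervention", followed by onboarding, intervention and maintenance. The stepped wedge was dropped because "staggered rollout required by stepped wedge design is no longer feasible to finish the study on time". The natural reading is one common sequence for all dyads.
- **Dependence.** Analysis, Aim 1 takes all eligible hospitalizations and plans to "adjust for the potential effect of clustering at the patient and provider level". No provider-by-period term is named.
- **Effect estimate.** The same section enters an intent-to-treat indicator with covariates from the Andersen model and states: "All hierarchical regression analyses will take these entropy balance weights into account". That sentence is sound in itself. It matters here because it shows that the hierarchical model carries the inference.
- **Time and external controls.** Study period: "We will adjust for time, or any health system interventions". The added controls are "drawn from the population of Medicare sepsis survivors not being cared for by any of the participating institutions", and one comparison group runs "across the entire study period".
- **Size.** Study sample gives a 23% readmission rate, a 7-point target reduction, 400 patients required per interval and 869 expected. It gives no significance level, sidedness, power, ICC or between-period correlation.

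**The concern.** A provider-level effect lets each dyad have its own stable readmission rate. It treats what remains between a dyad's baseline and intervention periods as patient-level noise plus the intervention. Rates at a hospital and its agency also move for local reasons such as staffing turnover, referral changes or a neighbouring programme. That movement enters the treatment contrast only five times, once per dyad, and does not average out as patients are added.

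National controls show what happened elsewhere over the same calendar time, which deals with shared shocks. They add no exposed dyads.

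At stake are the p-value and confidence interval for the primary outcome. Both would be too favourable, and ordinary local drift could pass for an intervention effect. This holds even if the mean model is a correct difference-in-differences.

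**Working it through.** **1. The plan's own figure.** Detecting 23% against 16% with independent patients and 80% power needs 396 per group at one-sided 5%, and 502 at two-sided 5%. The stated 400 therefore matches an individual-patient formula with no visible allowance for clustering, and only if the test is one-sided. At two-sided 5%, 400 per group gives 70.6% power.

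**2. Inputs for the type I error.**
- From Study sample: 5 dyads, 869 patients per period (869/5 ≈ 174 per dyad), rate p = 0.23, so p(1−p) = 0.1771.
- Assumed: equal dyad sizes, two periods compared, two-sided 5%, ICC 0.005 to 0.02, and between-period correlation c from 0.8 to 0.6. Here c is the share of the between-dyad variance that is common to both periods.

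**3. Formulas.**
- Variance with a provider intercept only: 2 × 0.1771/869 = 0.000408, so SE = 2.02 points.
- Dyad-by-period variance: s² = ICC × (1−c) × 0.1771.
- True variance: 0.000408 + 2s²/5. National controls would add a small term, ignored here; they do not reduce the first term.
- SE ratio r = √(true variance/0.000408). Type I error = 2 × [1 − Φ(1.96/r)].

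For ICC 0.01 and c = 0.8: s² = 0.000354 (s = 1.88 points) and 2s²/5 = 0.000142. True SE = √0.000549 = 2.34 points, r = 1.16, 1.96/1.16 = 1.69, and the error is 9.1%.

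| ICC | c | s (points) | True SE (points) | r | Type I error |
|---|---|---|---|---|---|
| any | 1 | 0 | 2.02 | 1.00 | 5.0% |
| 0.005 | 0.8 | 1.33 | 2.19 | 1.08 | 7.0% |
| 0.01 | 0.8 | 1.88 | 2.34 | 1.16 | 9.1% |
| 0.02 | 0.8 | 2.66 | 2.63 | 1.30 | 13.2% |
| 0.02 | 0.6 | 3.76 | 3.12 | 1.55 | 20.5% |

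More patients make it worse. In the last row, 400 per period instead of 869 gives 12.6%, because sampling error shrinks and drift does not.

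**4. Simulation.** Null trials (4,000 per setting, 174 patients per dyad-period, logit-scale random effects, an assumed 300 external providers, and a common period shift removed by those controls) gave these rates for the provider-intercept test:
- c = 1: 5.2% to 5.6%.
- c = 0.8: 7.2% (ICC 0.01), 10.6% (0.02) and 18.0% (0.05).
- c = 0.5: 10.8% (ICC 0.01), 16.9% (0.02) and 31.3% (0.05).

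The ICC is on the logit scale here, so the figures run somewhat below the formula.

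**5. Alternatives.**
- Uncorrected cluster-robust z-test: with five treated clusters its error is about P(|t₄| > 1.96 × √(4/5)) = 15.4%. Simulation gave 14% to 17% whatever the ICC.
- Provider-by-period variance estimated from the external providers: 4.5% to 5.9%.
- t-test with 4 df on the five dyad changes: 3.9% to 5.3%.

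**The case against.** **The article does not fix the model.** It never says random intercept only, z-test or uncorrected robust error, and a condensed article may leave degrees of freedom and random-effects detail to an analysis plan. This stands as a limit on certainty. Even so, the article does state a dependence structure, at patient and provider level, and that structure followed as written omits the variance in question.

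**Local drift is already adjusted for.** Time, health-system interventions and patient covariates are to be adjusted for, and the Discussion adds treatment indicators in the control and onboarding data as specification checks. These can reduce the residual variance, and the ICC range above makes no explicit allowance for them. They do not put what remains into the standard error.

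**Stronger readings a reader might infer, which the documents do not support:**
- That the trial's false-positive rate is 8% to 20% instead of 5%. ICC, between-period correlation and even the nominal level are unstated. The rate is 5% if the correlation is 1 or the missing term is fitted.
- That the analysis ignores clusters. It commits to provider-level clustering.
- That the simultaneous start causes the inflation. Concurrent controls and time adjustment handle shared shocks; only dyad-specific change remains.
- That the large control pool shrinks the error of the effect. The 2.02-point SE is the dyads' own before-after error, to which controls add a little. The pool is also what makes the remedy possible.

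**Conclusion.** The concern holds as a conditional fault in the stated dependence structure. Clustering at patient and provider level leaves dyad-by-period variation out of the standard error, and with five exposed dyads the test is anti-conservative whenever that variation exists.

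Under the assumptions in the working, the type I error is about 7% to 20%, within a wider span from 5% (no dyad-specific change) to above 30% (larger variance). Switching to an uncorrected cluster-robust test would not help, at about 15%. Confidence is medium, because the variance components are unknown and a fuller plan might already contain the missing term. The change is worth making since it needs only analysis work.

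**What to change.** In Analysis, Aim 1, add a provider-by-period random effect, defined at the hospital-agency dyad, to all Aim 1 hierarchical models. Estimate its variance with the non-participating national providers, and base the p-value and 95% CI for the intent-to-treat indicator on that model. State the significance level and sidedness. This assumes that period-to-period variation in the dyads resembles that in the national providers, so the plan should say how comparable providers (for example by volume) are chosen.

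Report two checks:
- The same adjusted, weighted contrast for many sets of five comparable non-participating hospital-agency pairs, as a placebo distribution. This should not be the sole primary method, because participating sites were chosen partly on relationships and commitment and may not be exchangeable with other pairs.
- A 4-df t-test on the five dyad contrasts.

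The cost is plan wording and computing time on claims data already to be requested, plus wider intervals. Under the assumptions used, the model-based CI becomes about 1.1 to 1.5 times as wide (r = 1.08 to 1.55). The 4-df interval becomes about 1.5 to 2.2 times as wide, since r is multiplied by 2.78/1.96 = 1.42. That width is why the t-test suits a check and not the primary test.

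### The stated Aim 1 regression names no participating-site main effect, so an unmeasured fixed difference between partner dyads and national controls can enter the treatment coefficient

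*Protocol article*

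**What the plan says.** The protocol article gives the dyads' own earlier patients as one comparison (Methods, Study design): "Sepsis survivors transitioned to the participating HHC agencies during the period before implementation serve as the usual care control group". To guard against historical threats it adds control groups from national Medicare data, within and outside the partner sites, for three windows: "1) one year prior to any contact with our team; 2) during the onboarding period, and 3) across the entire study period". The same section drops the stepped wedge and its staggered rollout.

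On the outside controls, the Aim 1 analysis section says: "These observations will be drawn from the population of Medicare sepsis survivors not being cared for by any of the participating institutions". Because they are not expected to resemble partner patients, "entropy balancing will be used to create sampling weights for these observations to produce balance on covariates". Then: "All hierarchical regression analyses will take these entropy balance weights into account". The terms of the regression follow: "In addition to an intent-to-treat indicator, the regression will include covariates specified by the Andersen Behavioral Model".

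Other parts of the model are stated elsewhere. Study period: "We will adjust for time, or any health system interventions, as well as patient covariates that may confound the findings using generalized mixed models". The Aim 1 analysis section also adjusts for clustering of patients and providers, and the conceptual framework places hospital and agency characteristics among the Andersen covariates. The Discussion promises extra checks with treatment indicators in the retrospective control data and in onboarding, to see whether dyads began early.

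On selection (Study sample, Aim 1): "Sites were selected based on our relationships with staff". That sentence goes on to ownership, commitment to an implementation team, size, geography and diversity.

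**The concern.** Without staggered rollout, treatment within the dyads coincides with being after go-live. The dyads' own before-after data cannot separate the intervention from calendar time, so the national controls must supply the time trend. Once they are pooled in, the comparison has two parts: how far the dyads changed, and how far they stood from the nation to begin with. Only the first is the intervention effect. A model whose treatment indicator is 1 for partner patients after go-live and 0 for everyone else, with no term for being a partner site, mixes the two unless covariates and weights explain the whole level difference.

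There is a reason to doubt that they do. Ownership and agency size are in Table 1, but relationships with staff and commitment are not. Organizational readiness is surveyed only among participating stakeholders, so it cannot balance national controls. The quantity at stake is the estimate for the primary outcome, 30-day readmission, in a non-randomised design.

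**Working it through.** The plan gives no figure that depends on this term, so there is none to reproduce. The check asks what share of a fixed partner-versus-national offset reaches the treatment coefficient.

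**Inputs from the article (Study sample, Aim 1).** 869 partner patients per period and 5 dyads: 869 / 5 = 173.8, taken as 174 per dyad-period. Planned effect: 7 points, from 23% to 16%.

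**Assumptions, not in the article.** ICC from 0.001 to 0.05; an offset of 3 points; one baseline period as large as the intervention period; a linear scale; period effects in the model.

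**No provider effect.** With period adjustment, 100% of the offset enters. If the dyads sit 3 points below the weighted controls and there is no true effect, a logistic fit gives an odds ratio of 0.837, that is −3.0 points. A true −7 reads as −10.0 with an offset of −3, and as −4.0 with +3.

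**Provider random intercepts.** Scale total variance to 1. Let T = ICC be the between-provider variance and e = (1 − ICC)/174 the variance of a dyad-period mean. Measuring from the national level, with the period effect removed, generalized least squares estimates the effect as the dyad's post mean minus w times its baseline mean, with w = T/(T + e). An offset d therefore contributes d(1 − w), and the share carried through is e/(e + T).

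| ICC | e | Share e/(e + T) | False effect at a 3-point offset |
|---|---|---|---|
| 0.001 | 0.00574 | 85% | 2.6 points |
| 0.005 | 0.00572 | 53% | 1.6 points |
| 0.01 | 0.00569 | 36% | 1.1 points |
| 0.02 | 0.00563 | 22% | 0.7 points |
| 0.05 | 0.00546 | 10% | 0.3 points |

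A full generalized least squares fit gave the same shares with 5 and with 1,000 national providers.

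**Longer baseline.** Divide the baseline e by the number of baseline periods. Adding six onboarding months to a baseline year (factor 1.5) gives 43%, 27.5% and 16% at ICC 0.005, 0.01 and 0.02. Two baseline periods give 36%, 22% and 12%.

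**Partner main effect added.** The share is 0% in every scenario, and a true −7 is recovered as −7.0.

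**Cost in precision.** Under the same simple model with many controls, the variance per dyad is e(e + 2T)/(e + T) with random intercepts and 2e with dyad fixed effects. The ratio is 2(e + T)/(e + 2T) = 1.36, 1.22 and 1.12 at ICC 0.005, 0.01 and 0.02. Taking square roots, the interval widens by about 17%, 11% and 6%.

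**The case against.** The strongest reply is that this is a condensed article and one sentence should not be read as the whole specification. The form of the provider adjustment is not given; it could be fixed effects, and the full protocol or analysis plan may say so. That stands as a limit on the point. A reader might infer that the model contains only an indicator and covariates, with nothing for providers. The article does not support that: it has a hierarchical structure, provider clustering, time adjustment and organizational covariates. Still, the sentence positively names terms, and none marks a participating site. The Aim 2 analysis section extends its hierarchical regressions in the same way, by treatment indicators for the intervention and maintenance periods.

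Second, a fixed offset cannot enter the dyads' own before-after comparison. True, but that comparison cannot separate treatment from time, which is why the national controls are there.

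Third, the Discussion's pre-period indicators could reveal a level difference. They are offered as a check for early adoption, outside the main model, and a standing site difference could be misread there as early adoption. The Discussion also promises matching if overlap fails, but matching too works on observed characteristics.

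Fourth, nothing in the article shows that partner readmission rates differ from weighted national rates. That stands: the ICC and the offset are assumptions, and a longer baseline shrinks the leak.

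**Conclusion.** The point holds as a weakness in the stated model that is cheap to repair. As named, the fixed terms leave a route for an unmeasured, time-constant partner-versus-national difference into the primary estimate. Entropy balancing does not close it, and random intercepts, if used, close it only partly. For a 3-point offset the false effect is 0.7 to 1.6 points at ICCs of 0.02 to 0.005, against a planned 7. These figures rest on the assumed ICC, offset and equal periods, and on a linear approximation.

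Two stronger readings do not follow. One is that the primary estimate is biased: the article gives neither the size nor the direction of any offset. The other is that the standard error is too small by a known amount. With five treated dyads and no named dyad-by-period variance this is a fair worry, but type I error figures from a simple before-after contrast in five dyads, with an assumed dyad-by-period spread, do not describe the pooled model. The degree of any understatement cannot be determined from the article.

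**What to change.** State in the primary Aim 1 model:

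- a participating-site main effect, or a fixed effect for each dyad;
- calendar-period effects shared with the entropy-weighted national controls;
- an intervention term equal to partner site × after go-live, so that it is a difference-in-differences contrast.

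Give the onboarding months their own indicator, or leave them out of the control data in the primary analysis, since the Discussion already accepts that dyads may start early. Use inference suited to five treated dyads; repeating the estimate on sets of untreated hospital-agency pairs from the national file (placebo inference) is one option among several. Keep the other comparisons as sensitivity analyses.

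The cost is wording and some computing time, because the baseline and national data are already being requested. The downside is the wider interval shown in the working. The contrast still assumes that partner and weighted national trends would have been parallel without the intervention, so the pre-period indicators should also be reported as a check on that.
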